## Abstract

Patients with coronavirus disease (COVID-19) commonly experience distressing and challenging respiratory symptoms. Interventions such as oxygen therapy, oral opiates, and traditional nebulizers like ipratropium bromide and salbutamol are variable in their efficacy, and therapy responses in patients are difficult to predict. The purpose of this study is to investigate the efficacy of nebulized fentanyl citrate on dyspnea, cough, and throat pain in patients with COVID-19 and evaluate the safety with any potential adverse events.

In COVID-19, about 59% of patients will exhibit cough, 35% generalized body ache and sore throat, and 31% dyspnea. Some methods such as nebulized lidocaine, magnesium sulfate, and systemic opioids have been used to manage the respiratory symptoms. It has been previously shown that fentanyl nebulizer has beneficial effect in improving shortness of breath in patients with chronic obstructive pulmonary disease. The proposed theory behind that was that fentanyl decreased the rate of spontaneous respiratory rate, diminished the brain stem chemoreceptor response to hypoxia and hypercarbia, in addition to exhibiting a modulating effect on the brain stem. Therefore, we hypothesize that nebulized fentanyl has superior effect in improving shortness of breath and relieving cough compared to normal saline, in addition to its advantageous throat pain relief, while exhibiting fewer side effects in patients with COVID 19 infection. Therefore, this phase-III, randomized, comparative, parallel assignment, single-blinded clinical trial aims at assessing the efficacy and safety of nebulized fentanyl to suppress cough, improve breathlessness, and relieve throat pain in patients with COVID-19.

## Introduction

1

Respiratory symptoms of coronavirus disease (COVID-19) infection can be distressing to the patients and challenging to the physicians who are managing them. Studies have revealed that COVID 19 virus utilizes the angiotensin converting enzyme, a protein expressed on the surface of many cells including respiratory mucosal epithelium, as a port of entry.^[1–3]^ Angiotensin-converting enzyme-2 is normally secreted in upper and lower respiratory epithelial cells; thus, angiotensin-converting enzyme-2 stimulation in COVID-19 infection will significantly surge pro-inflammatory mediators and mucosal secretions, leading to dyspnea (breathlessness), cough, and throat pain.^[4,5]^

This protein also acts as a pro-inflammatory mediator, which contributes to increased respiratory secretions in respiratory infections, and some of the other symptoms, predominantly, dyspnea, cough, and throat pain.^[6,7]^ These symptoms variably respond to medical interventions such as oxygen therapy, oral opiates, ipratropium bromide and salbutamol nebulizers. Physicians commonly use antihistamines and antitussive medications to suppress cough. However, these cough medications cannot be delivered to the respiratory system in a nebulized form. The National Institute For Health And Care Excellence guidelines recommend using opioids in managing cough and shortness of breath in COVID 19 patients.^[8]^

Alternative medications to manage cough were nebulized lidocaine, magnesium sulfate, and systemic opioids.^[9]^ However, side effects of these medications make their use limited. For example, systemic opioids were associated with sedative effect, dizziness, nausea, vomiting, constipation, physical dependence, tolerance, and most seriously, their effect on depressing the respiratory drive.^[10]^ On the other hand, the nebulized opioids can presumably exhibit their desired effect while lacking many of the systemic side effects, by binding to the receptors (μ, κ, and δ) and some active peptides (enzymes necessary for activation of opioids) already present in the lung and small airways.^[11–14]^ Compared to morphine and dihydrocodeine, nebulized fentanyl is more potent with less depressing effect on the respiratory drive, and interestingly, with an equal potency to its intravenous form. Nebulized fentanyl as proven to relieve shortness of breath in patients with chronic obstructive pulmonary disease due to its effect on decreasing the rate of spontaneous respiratory rate, diminishing the brain stem chemoreceptor response to hypoxia and hypercarbia, and modulating the activity of the brain cortex.^[15]^

Thus, based on the above evidence, we hypothesize that nebulized fentanyl may suppress cough, respiratory drive, improve breathlessness or dyspnea with the added advantage of relieving throat pain with minimal adverse effects in COVID-19 patients. This is a novel study as there is no literature on using nebulized fentanyl in COVID-19 or other viral infections to suppress cough, relieve breathlessness or dyspnea, and relieve throat pain.

## Objectives

2

Primary objectives: To assess the efficacy and safety of nebulized fentanyl to suppress cough, respiratory drive, improve breathlessness, and relieve throat pain in patients with COVID-19.

Secondary objectives: Overall patient outcomes (intensive care unit [ICU] or hospital stay and mortality).

Hypothesis: Nebulized fentanyl is effective and safe in providing symptomatic relief of cough, improving breathlessness, and relieving throat pain in patients with COVID-19, which is superior to saline nebulization.

## Trial design

3

This is a phase-III, randomized, comparative, parallel assignment, single-blinded clinical study.

## Methods: participants, interventions, and outcomes

4

### Study setting

4.1

The study will take place in the medical ICU in Hazm Mebaireek General Hospital in Qatar.

### Eligibility criteria

4.2

Age: 18 to 65 years;Confirmed diagnosis (COVID-19) – positive polymerase chain reaction;Tachypnea (respiratory rate >30/min);Ability to provide informed consent and perform all study procedures.

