##### Throat pain

4.4.1.2

Throat pain will be graded by the Numerical Rating Scale, in which patients will be asked to circle the number between 0 and 10 that fits best to their pain intensity. Zero usually represents “no pain at all”, whereas the upper limit represents “the worst pain ever possible”.^[17]^

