##### Cough

4.4.1.3

The cough severity score represents a simple instrument, using a 10-point scale, where the patient can indicate the severity of their cough between the 2 extremes: 1 for no cough while 100 mm is the most severe cough.^[18]^

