### Sample size & recruitment

4.6

After randomizing the selected patients, a total of 200 patients will be recruited using the sequentially numbered, opaque, sealed envelope (SNOSE) technique: the randomization group will be written on paper and preserved in an opaque sealed envelope. A serial number will be printed on the envelope. Once the patient has agreed to participate, the investigator will open the sealed envelope and allocate the patient to the appropriate treatment group.

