### Statistical methods

5.5

A well-structured case report form will be prepared and created to collect the essential data in line with the research study design and goals. Lead research investigators will conduct and maintain data quality in terms of completeness, verification, correctness, security, and confidentiality of data. Participants will be reassured that no personal identification will be used in scientific presentations or publications, that the anonymity and confidentiality of the study results will be maintained, and that their data will be kept confidential and accessible only to the study research investigators and authorized personnel from the research ethics committee.

The chi-square^[2]^ test and the Fisher exact test will be used to evaluate categorical data, if appropriate. The unpaired ‘*t*’ or Mann–Whitney *U* test will be used to compare continuous variables (quantitative data) between the 2 independent groups. The findings will be displayed together with the relevant 95% confidence interval. In addition, if necessary, other relevant regression models will be employed to examine and quantify the impact of various variables on primary and secondary outcome measures. Using appropriate statistical graphs, pictorial presentations of the relevant data will be created. All *P* values reported will be two-tailed, with *P* values less than .05 deemed statistically significant. All statistical analyses will be performed using the statistical software program SPSS 25 (SPSS Inc., Chicago, IL).

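### Cough and throat pain are primary outcomes, but entry requires neither and the stated test ignores pre-dose status, so symptom-free patients dilute both comparisons, throat pain most

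*Protocol article*

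**What the plan says.** All references are to the protocol article.

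- **Objectives (section 2).** The primary objective is "To assess the efficacy and safety of nebulized fentanyl to suppress cough, respiratory drive, improve breathlessness, and relieve throat pain". The hypothesis is superiority over saline in relieving these symptoms.
- **Eligibility (4.2) and exclusions (4.3).** Beyond age, a positive PCR and ability to consent, the one symptom-related criterion is "Tachypnea (respiratory rate >30/min". Neither section asks for cough, throat pain or a minimum score on either scale.
- **Throat pain (4.4.1.2).** On this primary outcome "patients will be asked to circle the number between 0 and 10 that fits best to their pain intensity", and zero means no pain.
- **Cough (4.4.1.3).** This is also primary. The ends of the scale are given as "1 for no cough while 100 mm is the most severe cough", so the written floor is 1, not 0.
- **Statistical methods (5.5).** The unpaired t or Mann–Whitney "test will be used to compare continuous variables (quantitative data) between the 2 independent groups". Regression is allowed only if found necessary. No use of pre-dose symptom status is stated.
- **Abstract.** In COVID-19, "about 59% of patients will exhibit cough, 35% generalized body ache and sore throat, and 31% dyspnea".
- **Sample size (4.6).** "a total of 200 patients will be recruited". Section 5.2 puts 100 in the fentanyl arm, which leaves 100 for saline.

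**The concern.** A patient with no throat pain before treatment cannot have throat pain relieved. If such patients stay at the floor in both arms, the expected difference between arms is no longer the benefit in patients who have the symptom. It is that benefit multiplied by the share who have it. The mixture of floor scores and symptomatic scores also widens the spread within each arm. Both effects push the standardized difference down.

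Two things are at stake. A real effect on throat pain, and to a lesser degree on cough, could be missed. And the all-patient difference does not describe what the objective promises, which is relief in patients who suffer from the symptom.

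**Working it through.** **Plan's own figure.** There is nothing to reproduce: no effect size, SD or power accompanies the 200. As a yardstick, 100 per arm at two-sided 0.05 gives 80% power for a standardized difference of (1.960 + 0.842) × √(2/100) = 0.40.

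**Inputs from the protocol.** 100 per arm; two-sided 0.05; prevalence p = 0.35 (body ache and sore throat jointly) and p = 0.59 (cough), both for COVID-19 in general.

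**Assumed, not in the protocol.** Symptomatic control patients average m = 5 points above the floor with SD 2; benefit δ = 1.5 points in symptomatic patients; symptom-free patients stay at the floor. Cough is treated as a 10-point scale. Only distance from the floor matters here, so a floor of 1 instead of 0 does not change the t-test figures.

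**Formulas.** Mean difference = pδ. Variance in an arm = p × SD² + p(1 − p) × mean², where the mean is 5 under saline and 3.5 under fentanyl. The two variances are averaged, and power comes from the noncentral t distribution.

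**Throat pain, p = 0.35.**
- Mean difference: 0.35 × 1.5 = 0.525.
- Variances: 1.40 + 0.2275 × 25 = 7.09 and 1.40 + 0.2275 × 12.25 = 4.19. Their average is 5.64, so SD = 2.37.
- Standardized difference: 0.525 / 2.37 = 0.22. Power 34%.
- Symptomatic patients only, 35 per arm: 1.5 / 2 = 0.75. Power 87%.

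**Cough, p = 0.59.**
- Mean difference: 0.59 × 1.5 = 0.885.
- Variances: 2.36 + 0.2419 × 25 = 8.41 and 2.36 + 0.2419 × 12.25 = 5.32. Their average is 6.87, so SD = 2.62.
- Standardized difference: 0.885 / 2.62 = 0.34. Power 66%.
- Symptomatic patients only, 59 per arm: 0.75. Power 98%.

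**Mann–Whitney, the plan's other named test.** By simulation with scores rounded to 0–10, all-patient power is about 14% for throat pain and 48–49% for cough. In the symptomatic subset it is 83% and 97%.

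**All patients, adjusted for symptom presence before dosing.** By simulation, power is 85–86% for throat pain and 97–98% for cough, essentially the subset figures. The adjustment simulated was for presence or absence; adjustment for the full score was not simulated.

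**Sensitivity (t test, m = 5).**

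| Prevalence | Benefit | All patients | Symptomatic only |
|---|---|---|---|
| 35% | 1 | 17% | 54% |
| 35% | 2 | 57% | 98% |
| 59% | 1 | 34% | 77% |
| 59% | 2 | 90% | >99% |
| 80% | 1 | 60% | 88% |
| 80% | 1.5 | 92% | >99% |

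With m from 4 to 6, all-patient power for throat pain runs from about 14% to 22% at a 1-point benefit and from about 45% to 73% at 2 points. For cough the ranges are about 27% to 43% and 81% to 97%.

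**The case against.** **The prevalences do not carry over directly.** The complements, 65% without sore throat and 41% without cough, might be read as facts about this trial. They are not. They describe COVID-19 patients in general, whereas the trial enrols medical-ICU patients breathing faster than 30 per minute. The same sentence puts dyspnea at 31%; carried over the same way, it would mean that 69% of these patients are not breathless. The 35% also joins body ache with sore throat. This objection stands: the true shares are unknown.

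**Cough is not badly hit.** A reader might infer that both comparisons lose most of their power and are dominated by zeros. For cough, 41% would be a minority, the written floor is 1, and t-test power at a 1.5-point benefit is still 66%. The strong wording fits throat pain only. This stands too.

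**Analysis sets and baseline handling may be in a fuller document.** The statistical methods name no analysis population, and adjusting for pre-dose status recovers the power in all patients. A subset analysis is therefore not the only remedy, and the fault need not lie in who is enrolled. That shapes the fix. It does not remove the point, because the protocol itself states the entry criteria, the primary outcomes and a plain two-group test, and leaves regression optional. Followed as written, they dilute both comparisons.

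**Symptoms may start after baseline.** Treatment lasts 48 hours, so some patients free of a symptom at entry may develop it. The calculation ignores this.

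**Conclusion.** The point holds in moderate form. The entry criteria, primary outcomes and stated test do not fit together for cough and throat pain, and the result is a diluted comparison. At the protocol's general COVID-19 figures, and with benefits of 1 to 2 points, all-patient t-test power is 17–57% for throat pain and 34–90% for cough, below what is reached when pre-dose status is used. The direction is robust: at every prevalence and benefit examined, the symptomatic comparison had at least the power of the all-patient one. The size is not robust. It rests on assumed means, SD and benefits, and on prevalences from a different population. If about 80% of enrolled patients have the symptom, the loss is small for benefits of 1.5 points or more. The documents do not support the conclusion that a real effect on cough would probably be missed, or that the entry criteria must change.

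**What to change.** 1. Rate cough and throat pain just before the first nebulization.
2. Make the all-patient comparison of each symptom adjusted for its own pre-dose score, in place of the plain two-group test.
3. Pre-specify, as the estimate of relief, the comparison among patients who have the symptom before dosing: throat pain above 0, and cough above the scale value that means no cough. This subset is fixed before treatment, so randomization still protects the comparison.

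The cost is one extra rating per scale and a few sentences in the protocol or SAP. The symptomatic estimate has a smaller denominator, roughly 35 per arm for throat pain and 59 for cough if the general figures applied, and its claim is limited to patients with the symptom. Eligibility and sample size need not change. The ethics section describes the study as still under review, so the change is easy to make. If nearly all patients turn out to be symptomatic, little is lost by having made it.

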### Exclusion criteria

4.3

History of allergy or adverse reaction to fentanyl or other opioids;Pregnancy;Active neuromuscular or musculoskeletal disease;Active malignancy;Morbid obesity (body mass index >40);Use of opioids in the previous 4 weeks;Inability to provide informed consent and perform all study procedures.

### Outcomes measures

4.4

#### Primary outcome measures

4.4.1

##### Breathlessness

4.4.1.1

The severity of breathlessness will be measured by the 10-point Borg scale [time frame: 15-minutes posttreatment]. Patients will be instructed to use this scale to rate their breathing difficulty. The scale is ranged from 0 to 10, where 10 is the maximum breathing difficulty.^[16]^

##### Throat pain

4.4.1.2

Throat pain will be graded by the Numerical Rating Scale, in which patients will be asked to circle the number between 0 and 10 that fits best to their pain intensity. Zero usually represents “no pain at all”, whereas the upper limit represents “the worst pain ever possible”.^[17]^

##### Cough

4.4.1.3

The cough severity score represents a simple instrument, using a 10-point scale, where the patient can indicate the severity of their cough between the 2 extremes: 1 for no cough while 100 mm is the most severe cough.^[18]^

##### Drug safety

4.4.1.4

Evaluate the safety of using the nebulized fentanyl with any potential adverse events.

#### Secondary outcome measures

4.4.2

The overall patient outcomes (ICU or hospital stay and mortality).

### Participant timeline

4.5

The trial is intended to last 1 calendar year following ethical clearance and will be extended yearly for a total of 5 years.

### Sample size & recruitment

4.6

After randomizing the selected patients, a total of 200 patients will be recruited using the sequentially numbered, opaque, sealed envelope (SNOSE) technique: the randomization group will be written on paper and preserved in an opaque sealed envelope. A serial number will be printed on the envelope. Once the patient has agreed to participate, the investigator will open the sealed envelope and allocate the patient to the appropriate treatment group.

## Methods: data collection, management, and analysis

5

### Type and classification of study – randomized control trial

5.1

Baseline matching: Demographic variables and comorbidities will be compared between both groups. The severity of the disease will be compared using sequential organ failure assessment scores.

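### Baseline SOFA should be a covariate named in advance for mortality and stay; the article uses it only for a between-arm comparison and leaves adjustment to an undefined need

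*Protocol article*

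**What the plan says.** All references are to the protocol article.

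- **Section 5.1**, under a heading that classifies the study as a randomised controlled trial: "Baseline matching: Demographic variables and comorbidities will be compared between both groups". The next sentence is the only mention of SOFA: "The severity of the disease will be compared using sequential organ failure assessment scores".
- **Section 4.4.2** makes ICU or hospital stay and mortality the secondary outcomes.
- **Section 5.5** sets the between-arm tests by type of data. For categorical data, the chi-square "test and the Fisher exact test will be used to evaluate categorical data, if appropriate". For continuous data, the unpaired t or Mann–Whitney U "test will be used to compare continuous variables (quantitative data) between the 2 independent groups". Mortality falls under the first and length of stay under the second.
- **Section 5.5** then adds that, "if necessary, other relevant regression models will be employed to examine and quantify the impact of various variables on primary and secondary outcome measures". This clause reaches mortality and stay. It names neither SOFA nor a model, and does not say what would make regression necessary.
- **Sections 4.6 and 5.2** give 200 patients, 100 of them on fentanyl, so 100 on saline. Allocation is by sealed envelope, and no stratification by severity is mentioned.

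**The concern.** SOFA is the article's own measure of disease severity, and severity is a natural predictor of death and length of stay. Yet no sentence links SOFA to an outcome analysis. The sections together state three things: a balance comparison described as matching, unadjusted tests as the default, and regression as an option without a trigger.

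The matching label does not fit the design. Allocation is random, and a comparison of arms at baseline matches nobody.

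Two things are at stake. The first is precision for mortality and stay, which a baseline covariate can improve with no new data. The second is pre-specification. As section 5.5 is worded, the team could decide for or against adjustment, and pick the covariates, after seeing the baseline table or the results. A reader of the final paper could not tell a planned adjusted result from a selected one.

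**Working it through.** **Inputs from the article.** 100 patients per arm; two-sided significance level 0.05 (section 5.5). The article states no effect size, standard deviation, event rate or power behind N = 200, so there is no figure of its own to reproduce.

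**Assumptions, not in the article.** Correlation r between baseline SOFA and a continuous outcome, 0.2 to 0.6. Control mortality 10% to 30%, treatment odds ratio 0.4, and odds ratio per standard deviation of baseline severity 1.5 or 2.5.

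**1. Are the unadjusted tests valid?** Let z be the standardised SOFA imbalance between arms. With no treatment effect, the unadjusted test statistic given z is approximately N(r·z, 1 − r²). Averaged over z ~ N(0, 1) it is N(0, 1), so the type I error is 5% for every r. Simulated null rejection rates for mortality were 4.4% to 6.2%, within simulation error of 5%.

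**2. Precision for a continuous outcome.** With a linear model for arm and SOFA, the variance of the treatment difference is multiplied by 1 − r², and the standard error by √(1 − r²). The equivalent unadjusted sample size is 200/(1 − r²). For reference, 100 per arm gives 80% unadjusted power at a standardised difference of (1.960 + 0.842)·√(2/100) = 0.396. The last column shows adjusted power at that same difference.

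| r | SE multiplied by | Equivalent N | Gain in patients | Power at 0.396 SD |
|---|---|---|---|---|
| 0.2 | 0.980 | 208 | 4% | 81.6% |
| 0.3 | 0.954 | 220 | 10% | 83.6% |
| 0.4 | 0.917 | 238 | 19% | 86.4% |
| 0.5 | 0.866 | 267 | 33% | 89.9% |
| 0.6 | 0.800 | 312 | 56% | 93.8% |

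Length of stay is usually skewed, so these figures are a guide for stay rather than an exact result.

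**3. Power for mortality.** Simulation, 2,000 trials per setting, treatment odds ratio 0.4. The unadjusted test is the pooled z test (equivalent to uncorrected chi-square). The adjusted test is the likelihood-ratio test from a logistic model with one standardised baseline covariate.

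| Control mortality | Covariate OR per SD | Unadjusted | Adjusted | Gain (points) |
|---|---|---|---|---|
| 10% | 1.5 | 34.8% | 36.3% | 1.5 |
| 10% | 2.5 | 34.9% | 36.9% | 2.0 |
| 20% | 1.5 | 58.9% | 60.9% | 2.0 |
| 20% | 2.5 | 53.2% | 57.1% | 3.9 |
| 30% | 1.5 | 74.0% | 75.3% | 1.3 |
| 30% | 2.5 | 64.8% | 70.3% | 5.5 |

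The gain is about 1 to 6 points. A much stronger covariate gives more. With SOFA ~ Poisson(4) (standard deviation 2), a log-odds of 0.7 per point (odds ratio exp(0.7 × 2) ≈ 4.1 per standard deviation) and a treatment odds ratio of 2.5, power rose from 59% to 70%. Nothing in the article supports a SOFA effect of that size.

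**The case against.** **The covariate model belongs to an analysis plan that is not shown.** This is partly right. The exact model for a secondary outcome is ordinary analysis-plan content, and its absence from an article is no fault. But sections 5.1 and 5.5 are not silent. They state the use of SOFA, name the default tests and make regression conditional. The point rests on those statements.

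**Regression is already provided for.** This stands as far as it goes: the clause covers secondary outcomes, so it would be wrong to say that mortality and stay can only be analysed unadjusted. What remains is that the clause fixes neither when adjustment happens nor for what.

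**A reader might infer that severity imbalance biases these outcomes.** The documents do not support that. Under sound randomisation a chance imbalance is part of the variation that the test already allows for. Given an imbalance of z = 1.9, the unadjusted type I error would be 7.7% to 15.3% for r = 0.3 to 0.6. But |z| falls between 1.90 and 1.96 in only 0.7% of trials. Averaged over all trials with |z| below 1.96, the error is about 4.7% down to 4.0% over the same range of r, which is below 5%.

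**A reader might also infer baseline significance tests, with balance declared at P above .05.** Section 5.1 names no test, P value or decision rule, and the threshold in section 5.5 applies to whatever P values are reported. Any estimate of how often a baseline table would show a spurious significant difference would need a number of tested variables, and their independence, that the article does not give.

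**The consequence is small.** This stands. The outcomes are secondary, nothing in the article sizes the trial for them, and the primary symptom ratings are outside this point.

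**Conclusion.** The point holds as an improvement in efficiency and pre-specification. It does not correct a bias or an invalid test.

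The stated plan uses a severity score it already intends to collect only for a descriptive purpose, under a label that does not suit a randomised design, and leaves adjustment to an undefined need. Fixing the adjustment in advance is a better method than the one stated. The size of the gain rests wholly on how well SOFA predicts outcome in these patients, which the article does not give. For a continuous outcome it is slight at r = 0.2 to 0.3 and material from about r = 0.5. For mortality it is modest throughout the plausible range examined. In a logistic model the gain appears as power, not as a smaller standard error of the odds ratio. The benefit of closing off a post hoc choice does not depend on any of these assumptions.

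**What to change.** - **Section 5.1:** remove the matching label. State that demographic variables, comorbidities and baseline SOFA will be described by arm, without significance tests.
- **Section 5.5, mortality:** make the main analysis a logistic regression on arm and continuous baseline SOFA. Report a SOFA-standardised risk difference with its 95% confidence interval.
- **Section 5.5, stay:** make the main analysis a model with arm and baseline SOFA. Its exact form can be set in the analysis plan before the data are seen.
- **For both outcomes:** remove the conditional wording, so that the adjusted analysis is done whatever the baseline table shows. Keep the chi-square or Fisher test and the t or Mann–Whitney test as sensitivity analyses.

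The cost is a change of wording and two extra model fits in SPSS, which the article already names. SOFA needs no new collection. One small downside is that the adjusted odds ratio is conditional on SOFA and differs from the crude one even under perfect balance. That is why the standardised risk difference should be reported beside it.
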